### Intervention

Participants within each facility are randomly assigned to one of three intervention groups. The intervention period is four months. Participants in the control group receive the usual care of their LTC unit throughout the four month time period, with the exception of scheduled outcome assessments. Participants in the Interpersonal Interaction group receive an approximately equivalent interpersonal interaction time (up to 30 minutes per day, five days per week) with research personnel as those in the Walking Program group. The interaction time occurs with the participant stationary. The participants in the Walking Program group receive an individualized, progressive, one-to-one supervised walking program provided by study personnel and supervised by a licensed physiotherapist. Each participant in this group walks once per day (up to half an hour), five days per week. The initial distance walked is initially determined for each individual based on how far the person can ambulate before visibly becoming fatigued or short of breath, reporting pain or requesting to sit down or rest. The distance walked and the intensity of the walking program during the four month period is gradually increased, as tolerated by the individual.

### Outcome measures

Outcome measures are completed at baseline. Re-assessment occurs after two months and four months of the intervention period, and at two and four months after the intervention period. The assessment of the outcome measures will be conducted by study personnel who are blind with respect to group allocation. The outcome measures include:

(1) Seniors Fitness Test (SFT) [30]. The SFT is a six-item battery, with demonstrated intra-rater and test-retest reliability and validity in older adults [30]. The SFT includes measures of dynamic upper (arm curls) and lower extremity strength (30-second sit-to-stand) and flexibility, aerobic endurance (2-minute step test), and mobility (8-ft walk test) [30].

(2) Berg Balance Scale (BBS). The BBS, a 14-item battery that assess a person's ability to safely perform several common daily living tasks, and is widely used as a measure of balance performance and fall risk assessment [31-33]. Performance on each item is rated on a scale from 0 (cannot perform the task) to 4 (normal performance of the task) and the maximum obtainable score is 56. The BBS has been reported to have excellent interrater and intrarater reliability and concurrent and discriminant validity [34].

(3) Grip strength. Grip strength is a reliable measurement when standardised methods and calibrated equipment are used, independent of evaluator or type of dynamometer, [35] and has been found to be a powerful predictor of disability, morbidity and mortality [36-38]. We will measure grip strength using a hand-held dynamometer using standard testing procedures. Three maximal repetitions (with 30 second rest between attempts) will be recorded for the dominant and non-dominant hand.

(4) Older American Resource Services (OARS) Activities of Daily Living Scale. The OARS is a brief, valid, and reliable instrument that is used as a clinical assessment of functional status [39]. The OARS ADL scale includes seven basic ADL items (eating, dressing and undressing, grooming, walking, getting in and out of bed, bathing, and continence), and seven instrumental ADL items (using the telephone, travel, shopping, meal preparation, housework, taking medicine, and management of finances) [39]. We will record the scores for the BADL items.

(5) Cornell Scale for Depression in Dementia (CSDD). We are assessing depression using the CSDD, a well-validated scale, with high sensitivity [40,41], and high inter-rater reliability and internal consistency [41]. The CSDD is designed for the assessment of depression in individuals with dementia and examines five areas: Mood-Related Signs, Behavioral Disturbances, Physical Signs, Cyclic Functions, and Ideational Disturbances [41].

(6) Geriatric Depression Scale (GDS) Short Form. We are also examining depression using the GDS Short Form, a well-known screen for depression in older adults which is widely used in community and LTC settings [42,43].

(7) Revised Memory and Behavior Problems Checklist (RMBPC). Behavioral problems will be assessed using the RMBPC, a valid and reliable 24-item measure for people with dementia, that includes three subscales, Memory-Related Problems, Affective Distress, and Disruptive Behaviour [44].

(8) Short Portable Mental Status Questionnaire [45]. The Short Portable Mental Status Questionnaire (SPMSQ) is a 10-item examination that has been found reliable and valid in distinguishing demented subjects from cognitively intact subjects. It is quick to administer and does not require much training, and we are using the SPMSQ to assess mental status.

(9) Coloured Analogue Scale [46]. This scale is being used to assess pain via patient self-report. Specifically, pain is rated by moving a plastic glide along a 14.5 cm long grid, varying in colour and width. That is, the scale is 1 cm wide at the bottom gradually widening to 3 cm at the top. Its colour is light pink at the bottom and progresses to a deep red colour at the top. The ends of the scale are anchored by the polar opposites “no pain” and “most pain”. As such, participants are presented with several visible cues for scaling the severity of their pain: length, width, colour and the anchoring words. The back of the scale has numbers ranging from 0 to 10 that are used by the assessor for the recording of pain intensity. This measure has been shown to be a valid index of self-reported pain with seniors who have mild to moderate dementia in that scores increase from baseline to painful situations [47].

(9) Gait speed (6 metre walk test). Participants will be asked to walk at their usual walking speed over a distance of 6 metres on the sensor mat of the GAITRite® system. The GAITRite® system (CIR Systems Inc., Clifton, NJ) is a portable walkway device, found valid and reliable for measuring selected spatial and temporal gait parameters [48-52] and allows concurrent videotaping of ambulation through a video camera interface. An additional two metres of walking will be added on each side to accommodate for acceleration and deceleration. The average of two attempts will be used to calculate walking speed in feet/second. Gait parameters, including gait speed, will be recorded.

### Other data collection

In order to control for confounding variables and to characterize the sample, the admission and most recent quarterly Resident Assessment Instrument-Minimum Data Set (RAI-MDS) [53] assessment data will be extracted. The RAI-MDS is a standardized LTC assessment tool designed to improve the care given to long-term care residents and it is used widely in Canada. The RAI-MDS data will be linked to the participants’ study ID number. The following RAI-MDS data will be included in the analysis: date of birth, race/ethnicity, gender, highest level of education, diagnoses on admittance, medications, health conditions; Cognitive Performance Scale; Depression Rating Scale; Index of Social Engagement; ADL Self-Performance Hierarchy Scale; Pain; Continence; Oral/Nutritional status; Communication; Mood and Behaviour Patterns; Physical Functioning and Structural problems; Activity Pursuit Patterns; Special Treatments and Procedures.

The incidence and nature of falls will be prospectively being collected using data from the Saskatoon Health Region Falls documentation protocol for the period of the intervention (four months) and for four months following intervention. Clinical staff records the nature and location of the fall, activity and symptoms at the time of the fall, and injuries resulting from the fall. Research assistants make copies of all falls records and add this to the research chart.

### Study organization

The clinical director of the study (principal investigator) is responsible for research personnel hiring and training, informed consent procedures, participant selection, clinical assessments, management of adverse events, data management, and general oversight of study procedures. A clinical research coordinator is carrying out many of the day to day tasks under the direction of the clinical director. A co-investigator will be responsible for the data cleaning and analyses.

### Data analysis

We hypothesize that participants taking part in the walking program will demonstrate maximal benefits compared to the no treatment control group (usual care) and the participants receiving only social interaction. We hypothesize that benefits of the walking program will include decreased fall rates, and improved balance, endurance, strength, mood, behaviour, activities of daily living and quality of life indices. As research has found that pleasant activities improve resident mood [54], we also hypothesize that participants in the social interaction group will demonstrate improvements in mood and other indices of quality of life.

The data will be analyzed using a random-effects multiple regression model [55]. The between-subjects factor will be condition (i.e., treatment and two control conditions). A random intercept for time (i.e., 5 measurement occasions) will be included to account for within-subject variation due to the repeated measurements. We will also evaluate model fit when a random slope for time is included in the model. Model fit will also be evaluated when the time x group interaction is included in the model. Additional covariates that may be included in the model are clinical measures from the RAI-MDS, such as the presence of comorbid conditions. Evaluation of model fit will be conducted using likelihood ratio tests and the Aikake Information Criterion [55]. Proportions of participants in the number of fall categories (e.g., non-faller, one-time faller, multiple faller) will be assessed using Pearson’s chi-square statistics.

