### Sample size

Sample size calculations assumed a moderate standardized effect size of 0.40 [28], a small value for the intra-class correlation (i.e., the proportion of variation accounted for by LTC units) of 0.05, and α = .05, power = .80. Sample size calculations determined that a sample size of 129 total participants will provide ample power for repeated measures analyses [29]. A balanced design will be adopted, with equal numbers of participants in each group. We will collect data from an additional 50 participants in order to account for attrition due to refusal or inability to continue with the protocol. As well, morbidity and mortality may account for some attrition.

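### Residents are randomised within facility and the sample size assumes variance between LTC units, but neither the regression model nor the falls test has a facility or unit term

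*Protocol article*

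**What the plan says.** Three sections of the protocol article bear on this.

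- **Intervention:** "Participants within each facility are randomly assigned to one of three intervention groups". The Discussion confirms that there are several facilities. Their number and size are not given.
- **Sample size:** an intra-class correlation of 0.05 is assumed, defined as "the proportion of variation accounted for by LTC units". The section also states that "A balanced design will be adopted, with equal numbers of participants in each group"; this describes the trial as a whole, not each facility.
- **Data analysis:** the regression has condition as the between-subjects factor, a random intercept, possibly a random slope for time, possibly a time by group interaction, and optional clinical covariates from the RAI-MDS. The random intercept is described thus: "A random intercept for time (i.e., 5 measurement occasions) will be included to account for within-subject variation due to the repeated measurements". Fall categories are compared with Pearson chi-square statistics.

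No facility or unit term appears in the regression or the falls test.

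**The concern.** The design treats facility as the setting within which groups are formed, and the sample size treats units as a source of outcome variance. The analysis gives that variance no place. An analysis that leaves out the grouping used in randomisation keeps between-facility variance in the error term. If allocation is balanced within facility, that variance does not enter the treatment contrast, so the standard error is too large. If it is not balanced, a chance difference in facility mix between groups stays in the estimate. The Discussion itself lists facility influences that could move outcomes, such as staffing, case mix and outbreaks. Falls are also documented by facility clinical staff.

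A second, smaller matter is in the sentence on the random intercept. It attaches the intercept to the measurement occasions, but its stated aim is to handle repeated measurements on the same person. An intercept per occasion gives all residents a shared visit effect. It does not link one resident's five records to each other.

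**Working it through.** **The plan's own figure.** The stated total is 129, or 43 per group. It can be neither confirmed nor refuted from the inputs given, because the type of effect size, the unit size and the within-resident correlation are not stated. Reading 0.40 as Cohen's f in a three-group one-way ANOVA gives 66. Multiplying by 1 + (20 − 1) × 0.05 = 1.95 gives 128.7, but this needs about 20 residents per unit, which the article does not state. What follows does not depend on 129.

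**Inputs**
- From the article: ICC 0.05 (stated for LTC units, applied here to facilities), two-sided α taken as 0.05, five occasions, three equal groups, effect 0.40 (read as a standardised difference for the power figures).
- Assumed: within-resident correlation ρ of 0.5 to 0.7; six facilities; equal allocation within each facility.

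**Facility omitted, balanced allocation.** Set the total variance at one visit to 1. The model without facility uses variance 1; the contrast really carries 1 − 0.05.
- One visit: SE ratio = 1/√0.95 = 1.026. Type I error = 2[1 − Φ(1.96 × 1.026)] = 4.4%.
- Five-visit mean: variance v = (1 + 4ρ)/5 and SE ratio = √(v/(v − 0.05)).
  - ρ = 0.5: v = 0.60, ratio √(0.60/0.55) = 1.044, type I error 4.1%.
  - ρ = 0.7: v = 0.76, ratio √(0.76/0.71) = 1.035, type I error 4.3%.

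**Simulation** (126 residents, six facilities of 21, seven per group in each, five occasions, 4,000 replicates per setting; walking against usual care, main effect, ICC 0.05):

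| ρ | Model | Type I error | Power at 0.40 |
|---|---|---|---|
| 0.5 | resident intercept, no facility | 4.1% | 66.5% |
| 0.5 | resident intercept + facility | 4.9% | 69.2% |
| 0.7 | resident intercept, no facility | 4.7% | 56.0% |
| 0.7 | resident intercept + facility | 5.4% | 57.8% |

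The gain is 2.7 points at ρ = 0.5 and 1.8 at ρ = 0.7. The Monte Carlo error on a 5% rate is √(0.05 × 0.95/4000) = 0.3 points.

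**Facility omitted, allocation not balanced within facility.** Randomising 86 residents to two groups of 43 without regard to six facilities, at ICC 0.05 and one measurement, gives a simulated type I error of 5.1%. Over repeated randomisations the test is then correctly sized. The loss is that any facility imbalance in the trial actually run is not adjusted for.

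**Random intercept coded literally on occasion.** A resident's records are then treated as independent.
- Group main effect: variance is understated by 1 + 4ρ. At ρ = 0.5, 2[1 − Φ(1.96/√3.0)] = 26%; at ρ = 0.7, 2[1 − Φ(1.96/√3.8)] = 31%. With facility balanced, the simulation gave 23.5% and 30.0%.
- Time by group (within-resident change): the SE is overstated by 1/√(1 − ρ), that is 1.41 at ρ = 0.5 and 1.83 at ρ = 0.7. Type I error falls to about 0.6% and 0.03%.

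So literal coding would distort the two tests in opposite directions.

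**The case against.** The strongest reply is that the effect of omitting facility is small and conservative: no false positives are created. That stands, and it bounds the size of the point. A reader might infer that ignoring clustering here inflates type I error, as it would if whole facilities were randomised. The article does not support that, because individuals are randomised within facilities.

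It is also fair that balance within facility is assumed. The Intervention section mentions no strata or blocks. The two possible harms are therefore alternatives: SEs are too wide to the extent that allocation is balanced, and imbalance goes uncorrected to the extent that it is not. The ICC is stated for units, and a facility term would capture only part of it if several units share a facility.

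An analysis plan that is not shown might add a site term, and the article presents its covariates as provisional. This reply has less force. The article lists its model terms, and that list does not match its own randomisation and sample size sections.

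On the random intercept, a reader might infer that the trial would run at a 26% to 31% false-positive rate. The article does not support that either. The sentence states a within-subject purpose, and the random slope for time that follows needs a grouping unit, most naturally the participant. The inflation would affect only the group main effect, and every correlation used is assumed. What remains is that the term as worded does not serve its stated purpose.

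**Conclusion.** The point holds as a modest mismatch between design and analysis. At ICC 0.05 with allocation roughly balanced within facility, SEs are about 2.6% to 4.4% too large, type I error is about 4.1% to 4.4% by formula, and some 2 to 3 points of power are lost. This rests on six facilities of equal size, ρ between 0.5 and 0.7, and the unit ICC applying to facilities. Without balance, the main cost is an unadjusted facility imbalance, whose size cannot be known in advance. The falls test has the same gap; its size was not calculated. The random-intercept sentence needs a secondary wording correction and does not show that an invalid model was intended.

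**What to change.** 1. **Regression models:** include facility as a fixed effect, or facility or unit as a random effect. Under six facilities a fixed effect costs five degrees of freedom (123 to 118 in the five-visit-mean analysis of 126 residents).
2. **Falls:** replace the plain Pearson chi-square with a comparison stratified by facility, for example a Cochran-Mantel-Haenszel test. This changes the named test but needs no new data, since residents are randomised by facility and facility is therefore known.
3. **Wording:** specify a random intercept for participant, with time as a fixed effect; if the random slope for time is kept, state that it is also by participant.

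The cost is a few sentences in the Data analysis section and the degrees of freedom above. Sample size and data collection do not change.

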### Procedures

After completing informed consent to participate in the study (or proxy consent by the appropriate SDM), all participants regardless of group will undergo a baseline assessment (see outcome measures section) conducted by trained study personnel prior to group allocation. Prior to enrolment in the specific study arm, family physicians are asked to optimize vitamin D levels, which will generally require obtaining vitamin D levels and prescribing 1,000 IU Vitamin D (if the participant is not already taking 1,000 IU or more) to control for potential influences on our study outcomes, and to be consistent with current recommendations [27]. Adherence with Vitamin D recommendations is monitored and reasons for intake problems are recorded.

Physical measures including respiratory rate, lying (after three to five minutes) and standing (after one minute) blood pressure, heart rate, as well as full height, knee-floor height, waist and calf circumference and weight are also collected at the beginning of the study, and except for height, measured also at week 8, week 16, week 24 and week 32, and whenever a medical concern arises. All adverse events (including falls, hospitalizations and surgeries) charted in nurses progress notes are collected, as are most recent full Resident Assessment Instrument-Minimum Data Set (RAI-MDS) and RAI-MDS updates, and the full, monthly medication administration record.

A licensed physiotherapist will assess the participant for fall risk and assign a visual analogue risk score ranging from negligible fall risk to highest fall risk, commenting on the reasons for the risk score assigned.

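### The pre-allocation baseline is modelled as a fifth outcome occasion and is not adjusted for, which costs power in the walking-versus-control contrasts

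*Protocol article*

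**What the plan says.** The Procedures section states that all participants "will undergo a baseline assessment (see outcome measures section) conducted by trained study personnel prior to group allocation". The Outcome measures section gives the schedule: "Outcome measures are completed at baseline. Re-assessment occurs after two months and four months of the intervention period", followed by two more assessments at two and four months after the intervention ends. That makes one assessment before allocation and four after it.

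The Data analysis section specifies a random-effects regression with condition (three arms) as the between-subjects factor. On the repeated measurements it says: "A random intercept for time (i.e., 5 measurement occasions) will be included to account for within-subject variation due to the repeated measurements". A random slope for time and the time-by-group interaction are each to be judged on model fit. On covariates it says: "Additional covariates that may be included in the model are clinical measures from the RAI-MDS, such as the presence of comorbid conditions". The baseline score of the outcome being analysed is not named as a covariate, and nothing sets the arm means equal at the first occasion.

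**The concern.** Baseline is measured before random allocation, so the true arm means are equal at that visit. A condition effect that applies to all five occasions nevertheless estimates a baseline difference between arms, and so spends information on a quantity known to be zero. If time-by-group is kept, the treatment contrast at a follow-up visit becomes follow-up minus baseline, compared between arms. That is less precise than a baseline-adjusted contrast for any correlation below 1. Below a correlation of 0.5 it is less precise than ignoring baseline altogether.

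At stake is power in a trial with about 43 frail and heterogeneous residents per arm, where the baseline scores needed to recover the loss are already being collected. The problem is separate from the choice to keep or drop the interaction on model fit: the loss remains when the interaction is kept and time is categorical.

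**Working it through.** **Inputs from the Sample size section.** Effect: "Sample size calculations assumed a moderate standardized effect size of 0.40". Clustering: "a small value for the intra-class correlation (i.e., the proportion of variation accounted for by LTC units) of 0.05". Error rates: "α = .05, power = .80". Size: "a sample size of 129 total participants will provide ample power for repeated measures analyses". Allocation is equal, so 129/3 = 43 per arm. A two-sided test is assumed, as sidedness is not stated.

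**The plan's own figure.** The 129 cannot be reproduced from the stated inputs alone. A plain two-group comparison at 0.40 needs 99 per arm, or 297 for three arms. Reading 0.40 as Cohen's f in a three-group analysis of variance gives 66, and 66 × (1 + 19 × 0.05) = 128.7, but only if there are 20 residents per unit. Averaging five occasions gives 132 if the within-person correlation is about 0.3. Each near match needs an input the article does not give, so 129 is neither confirmed nor refuted. What follows compares two analyses of the same data and does not test the 80% claim.

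**Assumptions.** SD = 1, equal correlation ρ between any two visits of the same person (as a random intercept implies), and 43 analysed per arm. Attrition and unit clustering are ignored in both models. The article gives no ρ, so a range is shown.

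**Variance per person, one follow-up visit.**
- Planned model with time-by-group kept: Var(Y − Y₀) = 1 + 1 − 2ρ = 2(1−ρ).
- Baseline-adjusted: 1 − ρ².
- Ratio: 2(1−ρ)/[(1−ρ)(1+ρ)] = 2/(1+ρ), which exceeds 1 for every ρ below 1.
- The planned variance exceeds 1, the value when baseline is ignored, whenever ρ < 0.5.

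**Power.** Noncentral t with 84 degrees of freedom and noncentrality 0.40/√(2v/43), where v is the variance above. At ρ = 0.5:
- planned, v = 1.00: 0.40/0.2157 = 1.855, power 0.450;
- adjusted, v = 0.75: 0.40/0.1868 = 2.142, power 0.562.

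| ρ | v planned | v adjusted | ratio | power planned | power adjusted |
|---|---|---|---|---|---|
| 0.3 | 1.40 | 0.91 | 1.54 | 0.341 | 0.485 |
| 0.4 | 1.20 | 0.84 | 1.43 | 0.388 | 0.516 |
| 0.5 | 1.00 | 0.75 | 1.33 | 0.450 | 0.562 |
| 0.6 | 0.80 | 0.64 | 1.25 | 0.536 | 0.630 |
| 0.7 | 0.60 | 0.51 | 1.18 | 0.658 | 0.728 |
| 0.8 | 0.40 | 0.36 | 1.11 | 0.826 | 0.863 |
| 0.9 | 0.20 | 0.19 | 1.05 | 0.984 | 0.988 |

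**Mean of the two on-intervention visits (months 2 and 4).** Planned: (1+ρ)/2 + 1 − 2ρ = 1.5(1−ρ). Adjusted: (1+ρ)/2 − ρ².
- ρ = 0.5: 0.75 against 0.50, power 0.562 against 0.737.
- ρ = 0.7: 0.45 against 0.36, power 0.780 against 0.863.

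**Cross-check.** Exact generalised least squares on the five-occasion model (normal approximation), with free arm baselines against a common baseline mean, gives month-4 power of 46% against 57% at ρ = 0.5 and 67% against 74% at ρ = 0.7. For the average of all four post-baseline visits, with a sustained effect, it gives 65% against 86% and 86% against 94%. The single-visit results agree with the table to about one point.

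**The case against.** The strongest reply is that this is a condensed article. It does not write out the fixed effects or define the contrast, and its covariate sentence is permissive. Free arm means at baseline are inferred from the condition term, not stated, and a five-occasion model with a common baseline mean would fit the same words. This stands in part: the inference is the ordinary reading of a condition main effect over five occasions, but it is an inference. It does not dispose of the point. The section goes beyond naming a model family: it fixes the number of response occasions, the between-subjects factor, the random effects, the type of covariate and the selection criteria. An analysis plan that followed it faithfully would carry the loss forward.

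Second, the planned analysis is standard and valid, and with time-by-group kept it is unbiased over randomisations and already uses baseline through change. That is correct; the cost is precision only. Sensitivity to regression to the mean after a chance baseline imbalance is the same cost seen conditionally, and should not be counted as a second harm.

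Third, the size depends on ρ, which is unknown and may be high for the well-standardised physical measures. This also stands: at 0.8 the single-visit gain is about 4 points and at 0.9 it is under 1.

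Fourth, making time-by-group conditional on fit may matter more. If it is dropped, the null baseline visit dilutes a sustained effect of 0.40 to 0.40 × 4/5 = 0.32. That is a separate weakness, and curing it alone would leave this one in place.

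**Conclusion.** The concern holds. Five occasions can be reached only by treating the pre-allocation baseline as a response, and the section names no adjustment for it. For every ρ below 1 the planned contrast has a larger variance than the adjusted one, by the factor 2/(1+ρ). At 43 per arm, effect 0.40 and two-sided 0.05, the single-visit power given up is about 14 points at ρ = 0.3, 11 at 0.5, 7 at 0.7, 4 at 0.8 and under 1 at 0.9. For averages over visits it is larger at the values of ρ most open to question: about 18 points for the mean of months 2 and 4 at ρ = 0.5.

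These sizes rest on an assumed ρ, equal correlation between visits, the interaction being retained, and no allowance for attrition or unit clustering. The direction does not depend on which ρ below 1 applies. The finding concerns efficiency, not bias, and does not show the stated sample size to be wrong. It is worth acting on because the improvement is nearly free.

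**What to change.** In the Data analysis section, specify one of two forms for each outcome measured at baseline:

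- the four post-baseline visits as the response, with condition, visit, condition-by-visit and that outcome's own baseline score as a fixed covariate; or
- all five occasions as the response, with the arm means constrained to be equal at the pre-allocation visit (no condition effect at that visit).

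State the adjustment in advance, outside the likelihood-ratio and information-criterion selection, so that it does not depend on model fit.

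The cost is about one sentence of wording, with no new data, visits or staff. With the covariate form, residents missing a baseline score on a scale need a simple stated rule. The constrained form avoids that and also keeps residents who have a baseline but miss follow-up visits. That is useful here, given the 50 extra participants planned for attrition.

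### The time-by-group interaction is left to a model-fit check, although without it the condition effect averages in a pre-allocation baseline and two off-intervention visits

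*Protocol article*

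**What the plan says.** The Data analysis section specifies a random-effects regression with condition as a three-level between-subjects factor and a random intercept over the five measurement occasions. Two further terms are candidates. The first is a random slope: "We will also evaluate model fit when a random slope for time is included in the model". The second is the interaction: "Model fit will also be evaluated when the time x group interaction is included in the model". Both are to be judged by likelihood ratio tests and AIC. The section names no contrast or visit as the test of the treatment effect, and does not say whether time enters the fixed part as a line or as categories.

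The visits are fixed elsewhere. Under Procedures, "all participants regardless of group will undergo a baseline assessment", and this takes place before allocation. Under Intervention, treatment lasts four months. Under Outcome measures, "Re-assessment occurs after two months and four months of the intervention period, and at two and four months after the intervention period". The occasions are therefore months 0, 2 and 4, with month 4 the end of the intervention, and months 6 and 8 off intervention.

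**The concern.** Randomisation after the baseline assessment makes the expected group difference at month 0 zero. When baseline is one of the outcome rows, the treatment effect is the departure of the groups from that common start, and this is what the interaction describes. A plan that treats the interaction as a candidate alongside an optional random slope lets the data decide whether the treatment effect is estimated as such.

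If the term is left out, the reported condition effect is an average over one visit that cannot show an effect, two on intervention and two after it has stopped. That answers a different question from what four months of walking achieves, and it is biased toward zero as an estimate of the end-of-intervention difference.

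**Working it through.** **The plan's own figure.** The Sample size section states "Sample size calculations assumed a moderate standardized effect size of 0.40", "a small value for the intra-class correlation" of 0.05, "α = .05, power = .80", and that "a sample size of 129 total participants will provide ample power for repeated measures analyses". I could not reproduce 129 from these inputs alone. A three-group ANOVA with f = 0.40 needs 66; multiplied by 1 + 19 × 0.05 = 1.95 this gives 128.7, but only with 20 residents per unit, which is not stated. The average of five repeated measures with d = 0.40 needs 43 per group only if the within-person correlation is about 0.30, also not stated. The figure is neither confirmed nor refuted. All that is used below is 129 / 3 = 43 per arm.

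**Assumptions.** Peak difference d = 0.40 SD; two-sided 5%; equal correlation ρ between all visits of a resident; no clustering and no attrition. The article gives neither ρ nor the course of the effect.

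**Step 1: dilution.** Without the interaction and with complete data, the condition effect is the mean of the five visit differences. If the interaction is included with time as a line, the fitted month-4 difference is twice the slope per visit, Σ t·e / 10 with t = −2, …, 2.

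| Assumed course at months 0, 2, 4, 6, 8 (× 0.40 SD) | Condition effect (SD) | Share of peak | Linear interaction: month-4 difference as share of true |
|---|---|---|---|
| 0, 1, 1, 1, 1 | 0.32 | 0.80 | 0.40 |
| 0, 0.5, 1, 1, 1 | 0.28 | 0.70 | 0.50 |
| 0, 1, 1, 0.5, 0.5 | 0.24 | 0.60 | 0.10 |
| 0, 0.5, 1, 0.75, 0.5 | 0.22 | 0.55 | 0.25 |
| 0, 0.5, 1, 0.5, 0 | 0.16 | 0.40 | 0 |
| 0, 1, 1, 0, 0 | 0.16 | 0.40 | −0.20 |

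**Step 2: power, walking against one comparator, course 0, 1, 1, 0.5, 0.5.** For single contrasts z = e / √(2v/43) and power = Φ(z − 1.96) + Φ(−z − 1.96).

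- Condition main effect: e = 0.24, v = (1 + 4ρ)/5. For ρ = 0.5, v = 0.60, z = 1.44, power 30%. For ρ = 0.7, v = 0.76, z = 1.28, power 25%.
- Categorical interaction, 4 df: noncentrality = (43/2) × Σ(e − ē)² / (1 − ρ), with Σ(e − ē)² = 0.16 × 0.70 = 0.112. This is 4.82 for ρ = 0.5 (power 38%) and 8.03 for ρ = 0.7 (power 61%).
- Baseline-adjusted month-4 contrast: e = 0.40, v = 1 − ρ². For ρ = 0.5, v = 0.75, z = 2.14, power 57%. For ρ = 0.7, v = 0.51, z = 2.60, power 74%.

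**Step 3: a case that favours the main effect.** Course 0, 1, 1, 1, 1 with ρ = 0.3. Main effect: e = 0.32, v = 0.44, z = 2.24, power 61%. Month-4 contrast: v = 0.91, z = 1.94, power 49%. The main-effect estimate is still 0.80 of the true difference.

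**Step 4: how often the fit check keeps the interaction.** In 3,000 simulated three-arm trials (ρ = 0.5, visit categorical), the term is retained by likelihood ratio test / AIC in 38% / 35% for course 0, 0.5, 1, 0.5, 0 and in 45% / 42% for course 0, 0.5, 1, 1, 1. Even with flexible coding of time, a real effect of this size would lose its interaction term in most such trials.

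**The case against.** The strongest reply is that the article says only that fit will be evaluated with the interaction included. It never says the term is dropped if fit does not improve, and detail may sit in a fuller plan. That is fair on the wording: dropping is the natural reading of a fit check, not a written rule. But the section is not silent. It describes a model-building step in which the treatment term has the same standing as an optional random slope.

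Several stronger readings are tempting, and the document does not support them:

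- *Time is entered as a slope, so the test is blind.* The only slope mentioned is an optional random one; five occasions could equally be coded as categories. Missing the effect altogether needs both linear coding and loss of the effect by month 8, as in the full-decay course above. With a build-up that persists (0, 0.5, 1, 1, 1) and ρ of 0.5 to 0.7, a linear interaction has 55% to 76% power, much the same as the month-4 contrast at 57% to 74%.
- *Two routes to significance inflate the type I error.* Two independent 5% tests would give 1 − 0.95² = 9.75%, but nowhere does the article say that a positive result on either term counts.
- *Every outcome is affected.* Fall categories are compared by chi-square, outside this model.
- *Baseline must be a covariate.* Modelling baseline as an occasion is accepted practice, provided the interaction is in the model.

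It is also true that the stated hypotheses name no time point. Month 4 is my proposal, chosen because it is the end of the intervention. Finally, the main effect is not always the weaker test, as Step 3 shows.

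**Conclusion.** The point holds in a limited form. For outcomes analysed with the random-effects model, the plan leaves the term that carries the treatment effect to a fit criterion. If the term is dropped, the condition effect estimates 0.40 to 0.80 of the peak difference over the courses tried. That dilution follows from the visit schedule and the pre-allocation baseline; its exact size depends on the assumed course. The power comparison also rests on assumed correlations and changes direction for an immediate, fully persistent effect with low correlation. The coding of time is an unstated detail that becomes harmful only if it is linear over months 0 to 8. Following the stated procedure can therefore give a misleading estimate, which makes this more than an omission of detail.

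**What to change.** For the continuous outcomes, fix one mean model before analysis:

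- group, visit as a categorical factor, and group by visit, always included;
- baseline handled either by adjusting for the outcome's baseline value or by constraining baseline means to be equal across groups;
- the month-4 contrasts of walking against usual care and walking against interpersonal interaction named as the treatment-effect test, with months 6 and 8 as durability contrasts;
- likelihood ratio tests and AIC used only to choose the random-effects or covariance structure.

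This changes wording and needs no new data. With baseline as covariate and four post-baseline visits, the interaction costs (3 − 1) × (4 − 1) = 6 parameters. The other cost is somewhat less power if the effect is immediate and fully persistent and within-resident correlation is low (49% against 61% in Step 3).
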